### Statistical analysis

Statistical analysis will be conducted by a statistician using SPSS version 22.0. Analyses will be performed based on intention-to-treat principles, and any missing data in the follow up visits will be imputed using multiple imputation.

Descriptive statistics will be used to summarize the baseline demographics and clinical characteristics for both groups. Missing values at follow-up visits or drop-outs in the two groups will be assessed to identify any potential bias.

For the primary outcomes, relative risk for the incidence of dermatologic toxicities with grade ≥2, including 95 % CIs obtained via normal approximation to the binomial distribution, will be analyzed for the two groups. The changes in nail color and skin color from baseline to 6 weeks will be compared between the two groups by independent sample *t* tests. Because participants will be randomized into the intervention group or wait-list group, little confounding is expected. However, potential confounding variables will be identified as those that differ among treatment groups at baseline and are significantly associated with outcomes. In case any potential confounders are identified, a logistic regression model and a multiple linear regression model will be used to analyze the binary and continuous outcomes, respectively.

In further analyses using measures at all time points, the relative effectiveness of the interventions, including all primary and secondary outcomes, will be assessed in repeated measures mixed models, using the generalized estimating equation (GEE) modeling method. The repeated measures regression models account for the correlations between individual measurements when repeated over time. The primary test of effect depends upon differing patterns of change (slope) over time; thus, differences in slope will be identified by significant interactions of intervention group with time. If the interaction terms are significant, then further analyses will use contrasts within the models to compare groups at each time point and to compare outcomes across time within each group.

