**Methods/design:**

This is a prospective assessor-blinded, parallel, randomized controlled trial. Patients with cancer at any stage who have completed chemotherapy within two weeks will be randomly divided into group A (YH0618) and group B (wait-list) using a 1:1 allocation ratio. The chemotherapeutic agents include taxanes or anthracyclines. Subjects assigned to group A will receive YH0618 soup 6 days a week for 6 weeks and uncontrolled follow-up for 6 weeks, while group B are required to wait for 6 weeks before receiving YH0618 intervention. The primary outcome of this study is the incidence of protocol-specified grade ≥2 dermatologic toxicities graded by NCI CTCAE Chinese version 4.0 and changes of fingernail color, face skin color and tongue color evaluated by the L*a*b system within 6 weeks. There are some secondary outcomes associated with dermatologic toxicity including fatigue and clinical objective examination.

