**Fig. 1 Fig1:**
[figure not shown]
Flow chart of the clinical trial

**Table 1 Tab1:** Trial process chart

	Before baseline screening	Baseline	Visit 1 Treatment phase	Visit 2 Treatment phase	Visit 3 Follow-up phase
Process items		0 day	3 weeks	6 weeks	12 weeks
Patients					
Inclusion and exclusion criteria	×				
Informed consent		×			
Demographics		×			
Medical history	×	×			
Randomization and allocation concealment		×			
Primary outcomes					
Grading of dermatologic toxicity		×	×	×	×
Objective skin, nail, and tongue color (L*a*b)		×	×	×	×
Secondary outcomes					
Fatigue measurement score		×	×	×	×
Routine blood test (WBC, HGB, PLT)		×	×	×	×
Liver function (ALT, AST, total protein, Alba)		×	×	×	×
Renal function (Cr and BUN)		×	×	×	×
Adverse events			×	×	×
Patients’ diary records		Every day during the study			

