### Estimation of sample size

The primary outcome in this study is the proportion of subjects with chemotherapy-induced dermatologic toxicity as measured by National Cancer Institute Common Terminology Criteria for Adverse Events (NCI CTCAE) specific grade ≥2. According to previous research, the incidence of NCI CTCAE specific grade ≥2 after the intervention is about 30 % [12]. Our pilot study showed that about 10 % of subjects would have NCI CTCAE specific grade ≥2 after taking the YH0618 soup; thus, the difference in proportion of subjects with dermatologic toxicity between the soup group and waiting-list control group is 20 %. The difference in proportion between the two groups will be examined by a Z-test. To achieve a type I error alpha = 0.05 and power (1 – beta) = 90 %, the minimal number of subjects needed in each group is 82. We estimated a 30 % attrition rate at the end of follow-up; hence, a sample size of at least 118 in each group (236 in total) is planned for this study.

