### Outcome evaluation

#### Primary outcome

The primary outcome of this study is the incidence of specific grade ≥2 dermatologic toxicities and changes of nail color, skin color, and tongue color after 6 weeks of intervention which will be graded by NCI CTCAE Chinese version 4.0 and evaluated by the L*a*b system, respectively.

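### The binary primary endpoint (grade ≥2 dermatologic toxicity) has no single time definition and no rule for patients who already have it at baseline

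*Protocol article*

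**What the plan says.** The protocol article describes the binary primary endpoint in four places.

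- **Abstract, Methods/design.** The primary outcome is the incidence of grade ≥2 dermatologic toxicities together with "changes of fingernail color, face skin color and tongue color evaluated by the L*a*b system within 6 weeks".
- **Primary outcome section.** "The primary outcome of this study is the incidence of specific grade ≥2 dermatologic toxicities", joined in the same sentence with "changes of nail color, skin color, and tongue color after 6 weeks of intervention".
- **Estimation of sample size.** "The primary outcome in this study is the proportion of subjects with chemotherapy-induced dermatologic toxicity" at grade ≥2, with rates of about 30% and 10% that are both described as post-intervention rates.
- **Statistical analysis.** "For the primary outcomes, relative risk for the incidence of dermatologic toxicities with grade ≥2" is to be estimated with a normal-approximation 95% CI. The colour changes are timed from baseline to 6 weeks; the relative risk is given no visit.

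Table 1 schedules "Grading of dermatologic toxicity" at baseline and at weeks 3, 6 and 12. Under Subjects, patients must have finished chemotherapy no more than 2 weeks before. The only skin-related exclusion is a history of dermatosis. The Background accepts that some symptoms persist after treatment stops.

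The Statistical analysis section also plans a logistic model, used only if a variable differs between groups at baseline and is significantly associated with outcome. A further GEE analysis uses all time points.

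**The concern.** Because toxicity is graded at weeks 3 and 6 as well as at baseline, a patient can be grade ≥2 at some point in the window and clear by week 6. An ever-within-the-window endpoint and a week-6 status endpoint are therefore different variables.

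The difference matters more here than in a prevention trial. Exposure to chemotherapy is over at entry and the hypothesis is that the soup ameliorates toxicity. A patient with grade ≥2 at baseline could be counted as an event from the start, left out of the at-risk set, or judged on status at week 6. The article does not say which. If baseline cases are automatic events, their recovery cannot contribute to the treatment effect. If the choice stays open, it can be made after the data are seen.

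A second, smaller matter is that baseline grade is likely to predict week-6 grade, yet the named relative risk does not use it unless the conditional rule happens to bring it in.

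**Working it through.** **Inputs from the sample size section:** control 30%, YH0618 10%, alpha 0.05, power 90%, 82 per group, 30% attrition, 118 per group. Sidedness is not stated; two-sided reproduces the figure. **Assumption:** the baseline prevalence b of grade ≥2 is not in the document, so it is varied from 10% to 50%.

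**Step 1. The plan's own figure.** Pooled Z-test without continuity correction:

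n = [1.960·√(2p̄(1−p̄)) + 1.282·√(p₁(1−p₁)+p₂(1−p₂))]² / (p₁−p₂)²

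With p₁ = 0.30, p₂ = 0.10 and p̄ = 0.20: [1.960·√0.32 + 1.282·√0.30]² / 0.04 = (1.109 + 0.702)² / 0.04 ≈ 82. Then 82/0.70 = 117.1, so 118 per group and 236 in total. Both figures reproduce, and power at 82 per arm is 90.0%. The arithmetic is sound for a plain proportion at one time point.

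**Step 2. Power under other readings, with 82 evaluable per arm.**

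Power = Φ{[(p₁−p₂)√n − 1.960·√(2p̄(1−p̄))] / √(p₁(1−p₁)+p₂(1−p₂))}

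*Reading A:* any grade ≥2 in the window, with baseline cases counted as events in both arms and 30% versus 10% in the rest. Then p₁ = b + 0.3(1−b) and p₂ = b + 0.1(1−b), so the difference shrinks to 0.2(1−b). For b = 30%: p₁ = 0.51, p₂ = 0.37, and Φ[(0.14·√82 − 1.960·√0.4928)/√0.483] = Φ(−0.156) = 43.8%.

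*Reading B:* new onset only, with baseline cases not at risk, so n = 82(1−b) at 30% versus 10%.

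| b | A: rates | A: RR | A: power | A: n per arm for 90% | B: n at risk | B: power |
|---|---|---|---|---|---|---|
| 10% | 37% vs 19% | 0.51 | 73.2% | 129 | 73.8 | 86.7% |
| 20% | 44% vs 28% | 0.64 | 57.0% | 188 | 65.6 | 82.5% |
| 30% | 51% vs 37% | 0.73 | 43.8% | 263 | 57.4 | 77.1% |
| 50% | 65% vs 55% | 0.85 | 25.6% | 503 | 41.0 | 62.3% |

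*Reading C:* status at week 6 in all patients at 30% versus 10% gives 90.0%, as planned.

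**Step 3. A limiting case (assumed).** Half the patients are grade ≥2 at baseline, there are no new cases, and 30% versus 10% remain at week 6. Counting baseline cases as events gives 50% versus 50%. Week-6 status gives 30% versus 10%.

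**Step 4. Value of using baseline grade.** Simulations of week-6 status used 82 per arm and marginal rates of 30% versus 10%. The first three rows had 20,000 replicates. Risks are listed for patients with and without grade ≥2 at baseline.

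| Baseline prevalence | Week-6 risk, control | Unadjusted | Mantel-Haenszel |
|---|---|---|---|
| 50% | 50% / 10% | 91.4% | 93.9% |
| 40% | 60% / 10% | 91.4% | 95.2% |
| 50% | 60% / 0% | 90.9% | 96.5% |
| 30% | 50% / 21% | 91.2% | 92.1% |
| 10% | 60% / 27% | 91.1% | 91.4% |

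Type I error under the null was 5.0% with either method. The SD of the chance difference in baseline prevalence between arms, at b = 30% and 82 per arm, is √(2·0.3·0.7/82) = 0.072, or about 7 percentage points.

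**The case against.** The best defence is that the main text already leans one way. The Primary outcome section says after 6 weeks, and the sample size section speaks of the proportion with toxicity after the intervention. On that reading the 82 per group reproduces. The competing phrase, "evaluated by the L*a*b system within 6 weeks", occurs only in a condensed abstract and sits beside the colour measures, so it may not be meant for toxicity at all. This stands as a guide to intent, but it does not settle the endpoint. If the phrase belongs to colour alone, the abstract gives toxicity no window. The Primary outcome section still says incidence, the relative risk still has no visit, and no section says how baseline cases count. The Background itself cites another trial's incidence over a 6-week treatment period, so a cumulative reading is not far-fetched.

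It is also fair that a within-6-weeks endpoint need not make every baseline case an event. It could mean new onset, or grade ≥2 at a post-baseline visit. Reading A is therefore one possibility among several.

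A reader might infer that the analysis ignores baseline grade altogether. The Statistical analysis section does not support that: baseline grade could enter the conditional logistic model, and the GEE uses all time points. Neither is a full answer. The conditional rule picks covariates by observed imbalance and significance, and moves from a relative risk to a logistic model. The GEE is presented as further analysis and takes in week 12, after group B has had the soup.

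**Conclusion.** The concern holds as a definitional defect. The plan does not consistently fix when the binary primary endpoint is assessed, and it does not say how patients with grade ≥2 at baseline count. This is the definition of the primary variable and the stated wordings differ, so it is more than detail left to a later document.

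At 82 per arm, power is 90% for week-6 status, about 87% down to 62% for new onset, and 73% down to 26% if baseline cases count as events. These ranges rest on an assumed baseline prevalence of 10% to 50% and, for the last two, on applying 30% versus 10% to patients without baseline toxicity. The document supplies no prevalence. It shows that baseline cases are possible, not that they are many.

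Two stronger inferences are not supported. The readings need not give opposite answers: the limiting case shows an effect under one and none under the other, with no reversal of direction. Leaving out baseline grade also does not bias the randomised comparison. It costs precision, from almost nothing to about 6 points of power in the scenarios simulated. The gain is largest when baseline prevalence is high and strongly tied to outcome. On its own that would be a minor point.

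**What to change.** Define the primary once, and repeat it in the abstract, the Primary outcome section, the sample size section and the Statistical analysis section: the proportion of all randomised patients with any protocol-defined dermatologic toxicity of grade ≥2 at the week-6 visit. State that patients with grade ≥2 at baseline are included and counted by their week-6 status. Replace the incidence and within-6-weeks wording to match. This agrees with the sample size rationale and the Primary outcome section, and leaves 82 and 118 per group unchanged.

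Pre-specify stratification by, or adjustment for, baseline grade ≥2 (yes/no), for example a Mantel-Haenszel relative risk with its 95% CI, in place of the conditional confounder rule.

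The cost is wording in the protocol and analysis plan, and in the registry entry if it carries the same text. Baseline and week-6 grades are already scheduled in Table 1, so no extra visits, measurements or patients are needed. The change should be made and dated before outcome data are compared by group.

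### A 12-week group-by-time slope is labelled the primary test, although the trial is sized on a two-proportion comparison and its primary outcome falls at week 6, before the control arm takes the soup

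*Protocol article*

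**What the plan says.** Estimation of sample size names the proportion with grade 2 or higher dermatologic toxicity as the primary outcome and states: "The difference in proportion between the two groups will be examined by a Z-test". It concludes that "the minimal number of subjects needed in each group is 82". Primary outcome, under Outcome evaluation, places the assessment after 6 weeks of intervention.

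Statistical analysis handles the same outcome in three steps.

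- For the primary outcomes it gives a relative risk with a 95% interval "obtained via normal approximation to the binomial distribution". The colour changes from baseline to week 6 are compared by t tests.
- If baseline confounders are found, it moves to logistic regression for binary outcomes.
- In a paragraph introduced as further analyses, it fits a GEE model to every time point and to all primary and secondary outcomes, and says: "The primary test of effect depends upon differing patterns of change (slope) over time". Group contrasts at individual visits follow only if the interaction is significant.

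Table 1 lists assessments at baseline and weeks 3, 6 and 12. Intervention and control conditions has group B wait for 6 weeks and then take the soup for 6 weeks.

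**The concern.** Two sections point to different primary tests. The sizing belongs to a comparison of two proportions and the primary outcome to week 6. The word primary is attached to a slope difference over a window whose last visit falls after the control arm has been treated. At week 12 the between-arm difference no longer contrasts soup with no soup. It contrasts earlier soup with later soup.

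Two things are at stake. An effect that is clear at week 6 could be missed by the test the article calls primary, and the significance gate would then block the model's own week-6 contrast. Conversely, if the tests disagree, either can be presented as the primary result.

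**Working it through.** **1. The plan's own figure.** Inputs from Estimation of sample size: "type I error alpha = 0.05" (sidedness not stated), power 90%, control rate 0.30 ("the incidence of NCI CTCAE specific grade ≥2 after the intervention is about 30" per cent), soup rate 0.10 ("about 10 % of subjects would have NCI CTCAE specific grade ≥2 after taking the YH0618 soup"). With a two-sided test and pooled variance:

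n = [1.96·√(2·0.2·0.8) + 1.2816·√(0.3·0.7 + 0.1·0.9)]² / 0.2² = (1.1087 + 0.7020)² / 0.04 = 81.97, so 82 per group.

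"We estimated a 30 % attrition rate at the end of follow-up": 82/0.7 = 117.1, so 118 per group and 236 in total. The stated size reproduces exactly, and it is the size for a single comparison of two proportions. No slope enters it.

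**2. The slope over all visits.** Assumptions, none of them stated in the article: time is linear; the soup gives benefit d after 6 weeks in either arm and d/2 after 3 weeks; the benefit persists in group A; visits are weighted equally; d is on the scale of the outcome. The advantage of A over B at weeks 0, 3, 6 and 12 is then 0, d/2, d, 0.

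- Mean time 5.25; deviations -5.25, -2.25, 0.75, 6.75.
- Sxx = 27.5625 + 5.0625 + 0.5625 + 45.5625 = 78.75.
- Sxy = -2.25·d/2 + 0.75·d = -0.375d.
- Slope = -0.375d/78.75 = -0.005d per week.

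Over weeks 0, 3 and 6 only: Sxx = 18, Sxy = 3d, slope = 3d/18 = +0.167d per week.

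**3. Range.** Let a fraction r of the week-6 difference remain at week 12. The slope is (6.75r - 0.375)d/78.75. A longer window also estimates a slope more precisely, so a fairer measure of signal is slope × √Sxx (equal variances and independent visits assumed).

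| Window | Slope per week | Slope × √Sxx |
|---|---|---|
| Weeks 0–6 | 0.167d | 0.707d |
| Weeks 0–12, r = 0 | -0.005d | -0.042d |
| Weeks 0–12, r = 0.5 | 0.038d | 0.338d |
| Weeks 0–12, r = 1 | 0.081d | 0.718d |

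The signal is kept in full only at r = 1, for example if group B gains nothing from the soup and group A's benefit lasts. At r = 0 it is about 6% of the weeks 0–6 signal (0.042/0.707), with the sign reversed.

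**4. Time modelled by visit.** If visit is a categorical factor, the interaction contains the week-6 contrast as one of its components, so the effect is not cancelled. It is still a joint test that includes week 12, and the week-6 contrast still waits on its significance.

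**5. The relative-risk interval.** All pairs of binomial outcomes were enumerated at equal rates of 10%, 20% and 30%, with zero cells counted as non-rejections. Rejection in favour of the soup, nominal 2.5%:

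| Method | 82 per group | 118 per group |
|---|---|---|
| Pooled Z-test | 2.5 / 2.5 / 2.5% | 2.6 / 2.5 / 2.5% |
| Interval on log RR | 1.9 / 2.1 / 2.3% | 2.1 / 2.4 / 2.4% |
| Interval on untransformed RR | 8.1 / 6.2 / 5.4% | 7.4 / 5.6 / 4.8% |

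On the untransformed scale the opposite tail falls to 0.0–0.4%, so total two-sided error is about 5.2–8.1%. At 30% against 10% with 82 per group, exact power is 0.911 for the Z-test and 0.897 for the log-scale interval.

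**The case against.** The intended order can be read from the text. The week-6 analyses come in the paragraph on the primary outcomes, and the GEE paragraph opens as further analysis. That is a fair reading and probably the intended one. It does not remove the contradiction, because the later paragraph covers the primary outcomes and attaches the primary label to the interaction.

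The slope arithmetic rests on a linear time effect and equal, lasting benefit, and the article states neither. The planned contrasts at each visit fit time modelled by visit just as well. This stands: the near-complete loss of signal is conditional. The label and the gate conflict with the week-6 outcome under either model.

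A reader might infer two stronger points.

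- **That the relative-risk interval doubles or triples the false-positive rate.** The article does not say the interval is formed on the untransformed scale. The usual log-scale interval is also a normal approximation and shows no inflation. Even on the untransformed scale, the two- to threefold figure concerns one tail only.
- **That the Z-test and the relative risk are rival tests.** They address the same null. With a log-scale interval their decisions differ in at most 1.2% of samples under equal rates of 10–30%, and in 1.4% at 30% against 10% with 82 per group. Testing a difference and reporting a relative risk is ordinary practice.

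**Conclusion.** The conflict lies between the week-6 two-proportion comparison on which the trial is sized and the all-visit group-by-time slope labelled primary. It should be resolved before analysis.

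Under linear time and equal, lasting benefit in both arms, the labelled test retains almost none of the week-6 effect (-0.005d against +0.167d per week), and its failure blocks the model's week-6 contrast. The loss shrinks as more of the difference survives to week 12 and vanishes if all of it does. With time modelled by visit, what remains is the wrong label and the gate.

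The unstated scale of the relative-risk interval is a minor clarification. It carries a risk of 4.8–8.1% one-sided error in favour of the soup if the untransformed scale were chosen, but it is not a demonstrated error of the plan.

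**What to change.** - Name one primary test for toxicity: the week-6 difference in the proportion with grade 2 or higher, by the Z-test used for sizing.
- Call the GEE group-by-time interaction secondary and restrict its between-arm version to weeks 0 to 6. Week 12 can be described within each arm.
- Do not make the week-6 contrast depend on the interaction being significant.
- State that the relative-risk interval is formed on the log scale or by the score method.

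The cost is wording in the analysis plan. No data, visits or patients are added, 118 per group stands, and the log-scale interval has nearly the same power as the Z-test.

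### Adjustment covariates are chosen from observed baseline imbalance and outcome association, so the primary model is not fixed in advance; the cost is a modest forgone gain in precision and an unclear effect measure

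*Protocol article*

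**What the plan says.** In the protocol article, Estimation of sample size rests the trial on a binary endpoint: "The primary outcome in this study is the proportion of subjects with chemotherapy-induced dermatologic toxicity", graded by NCI CTCAE at grade ≥2. The planning rates are 30% in the wait-list group and 10% with the soup. On the test it says: "The difference in proportion between the two groups will be examined by a Z-test".

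Statistical analysis then gives, for the primary outcomes, a relative risk with 95% confidence interval for grade ≥2 toxicity, and independent-sample t tests on the change in nail and skin colour from baseline to 6 weeks. It remarks that randomisation should leave little confounding, but adds that "potential confounding variables will be identified as those that differ among treatment groups at baseline and are significantly associated with outcomes". In that event, "a logistic regression model and a multiple linear regression model will be used to analyze the binary and continuous outcomes, respectively".

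The section lists no candidate variables and gives no threshold for differing at baseline. It does not say whether the regression takes the place of the relative risk and t tests or stands beside them.

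**The concern.** This is a rule the protocol states, not a detail left to an analysis plan; a plan that followed the protocol would inherit it. Three things are wrong with it.

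- Allocation is randomised 1:1, so baseline differences between the groups arise by chance. Observed imbalance is a poor reason to adjust, and its absence is a poor reason not to: a strong predictor of the outcome, such as the baseline value, improves precision whether or not it is imbalanced.
- The second condition, association with the outcome, uses outcome data. Which model carries the primary result is therefore settled only after the outcomes are known.
- For the binary outcome, a logistic model by default estimates a conditional odds ratio, which is a different quantity from the planned relative risk. The text plans no conversion back to the risk scale.

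At stake are a primary result whose model and possibly effect measure depend on the data, and some precision given away although the baseline measurements are already scheduled.

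**Working it through.** **1. The plan's own figure.** The inputs are from Estimation of sample size: rates 0.30 and 0.10, alpha 0.05 (taken as two-sided, which is not stated), power 0.90. With the pooled two-proportion formula, mean rate 0.20:

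n = [1.960·√(2·0.20·0.80) + 1.282·√(0.30·0.70 + 0.10·0.90)]² / 0.20² = [1.109 + 0.702]² / 0.04 ≈ 81.96, so 82 per group.

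With 30% attrition, 82/0.70 = 117.1, so 118 per group and 236 in total. The stated figures reproduce. Power of this unadjusted test is 0.900 at 82 and 0.974 at 118 per group.

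**2. Effect measure at the planning rates.** RR = 0.10/0.30 = 0.333. OR = (0.10/0.90)/(0.30/0.70) = 0.259.

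**3. The rule on the binary outcome, by simulation.** There were 3,000 runs per scenario. The following are assumptions, not figures from the article: 10 independent normal baseline covariates; 0, 2 or 3 of them prognostic, with log odds ratio 0.5 or 0.8 per SD; both selection conditions applied at p < 0.05; the logistic result replaces the relative risk when a covariate is selected. Power at 82 per group:

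| Prognostic covariates | Unadjusted RR | Stated rule | Prespecified logistic |
|---|---|---|---|
| None | 0.897 | 0.895 | 0.904 |
| 2, log OR 0.5 | 0.900 | 0.900 | 0.921 |
| 2, log OR 0.8 | 0.889 | 0.890 | 0.939 |
| 3, log OR 0.8 | 0.899 | 0.900 | 0.950 |

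The Monte Carlo standard error is about √(0.9·0.1/3000) = 0.0055. The rule is within 0.2 points of the unadjusted relative risk in every row. Prespecified adjustment gains 0.9, 2.1, 4.9 and 5.0 points over the rule. The first of these is not a real gain, since the plain Z-test reached 0.912 in the same scenario, so the range is about 0–5 points. At 118 per group the rule gives 0.973–0.983 and prespecified adjustment 0.973–0.992.

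The type I error of the rule, over both sample sizes, was 0.037–0.050. The switch to logistic regression occurred in about 2–4% of trials with no prognostic covariate and 9–17% with two or three.

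**4. A continuous outcome.** Assumed: 82 per group, effect 0.45 SD, baseline–outcome correlation 0.6, equal variances. Power follows from the noncentral t with noncentrality (0.45/SD)·√(82/2):

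- Follow-up value alone: SD 1, noncentrality 2.88, power 82%.
- Change score, as planned for colour: SD √(2·(1 − 0.6)) = 0.894, noncentrality 3.22, power 89%.
- ANCOVA: SD √(1 − 0.6²) = 0.8, noncentrality 3.60, power 95%.

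With the follow-up value as the unadjusted analysis, simulation gives the rule 83% power and a type I error of about 4%. The apparent gap to ANCOVA is then 95 − 82 = 13 points. But the protocol compares changes from baseline, which already use the baseline value, so the relevant gap is 94.7 − 89.3 = about 5 points.

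**The case against.** The strongest reply is that the rule does little harm. It triggers seldom, the article itself expects little confounding, and the statisticians are to be kept blind to group (Randomization and blinding; Discussion). The relative risk is stated without condition, so the regression may be read as an added analysis. No test of baseline differences is named, only that variables differ. Linear regression keeps the mean-difference scale, so any change of effect measure touches the binary outcome alone.

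Most of this stands, and it rules out three stronger readings that a reader might infer.

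- *The rule inflates type I error.* Applied as written, it is at or slightly below the nominal level. Reporting whichever of the unadjusted and adjusted results had the smaller p-value would give about 8% in the continuous setting, but the article does not plan that.
- *The rule costs planned power.* It matches the unadjusted analysis on which the trial was sized. Only the gain from fixed adjustment is lost.
- *The protocol announces a switch to an odds ratio.* It never names one. The odds ratio is inferred from the usual output of logistic regression, and a standardised relative risk could be derived from the same model, although none is planned.

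What the reply does not remove is the dependence of the model on outcome data. Blinding to group limits steering but does not fix the model in advance. Reading the regression as supplementary is possible, but the text does not settle it.

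**Conclusion.** The concern holds in a limited form. The protocol selects adjustment covariates from the trial data and leaves open whether the resulting regression replaces or supplements the unadjusted relative risk and t tests. The primary model, and for the binary outcome perhaps the effect measure (0.33 or 0.26 at the planning rates), is therefore not determined beforehand.

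The measurable cost is modest: about 0–5 points of power forgone at 82 per group for the binary outcome, and about 5 points against the change-score t test for a colour outcome. Both figures rest on assumed prognostic strength, for which the article gives no data; the colour figure also assumes a correlation of 0.6 and an effect of 0.45 SD. Neither type I error nor the planned 90% power is shown to be harmed. The change should be made because it is a free improvement and fixes the primary analysis, not because the design fails without it.

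**What to change.** - Delete the rule that picks covariates by baseline difference and outcome association.
- Prespecify adjustment for the baseline value or grade of the outcome, whatever imbalance is observed. Drug class may be added, coded as taxane, anthracycline or both, because the eligibility wording does not make the two exclusive.
- Use ANCOVA for the colour outcomes.
- Report the binary outcome as an adjusted relative risk or risk difference, by modified Poisson regression or by standardisation from a logistic model.
- Name this as the primary analysis and label any other model a sensitivity analysis.

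The cost is wording, settled before unblinding. Table 1 already schedules toxicity grading and colour at baseline, and drug class is known from the inclusion criteria. The sample size stays at 118 per group.
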